## Trial objectives

The primary objective is to assess the safety and efficacy of 8 weeks of SCiP™ therapy during ABNT compared to sham (inactive) neuromodulation during ABNT in improving voluntary sensorimotor function measured on the GMFM88 scale in children with CP. The secondary objective is to assess the safety and efficacy of short-term (8 weeks) vs. long-term (16 weeks) SCiP™ in conjunction with ABNT in improving voluntary sensorimotor function (GMFM88 score). We hypothesize that children who undergo SCiP™ neuromodulation therapy in conjunction with ABNT will demonstrate a statistically greater improvement in voluntary sensorimotor function as assessed by GMFM88 scores, compared to subjects undergoing sham modality in conjunction with ABNT. The proposed clinical trial was discussed with the US FDA via a virtual sprint discussion owing to the breakthrough device status; and SpineX and the agency have reached an alignment on the clinical trial design, primary and secondary outcomes, sample size and safety outcomes.

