### Primary outcomes

All assessments will be performed by a trained pediatric physiotherapist who will evaluate all participants at the site. The therapist will be thoroughly trained during the site initiation visit and provided with an illustrated guidebook to ensure consistency across sites. The assessing therapist will be blinded to the group assignments.

Gross Motor Function Measure-88 (GMFM88): GMFM88 is a standardized observational instrument designed and validated to measure change in gross motor function over time in children with CP using a 4-point Likert scale for 88 items across five dimensions: (a) lying and rolling, (b) sitting, (c) crawling and kneeling, (d) standing, and (e) walking, running, and jumping. The participant will complete a number of gross motor activities, depending on the age and ability (Russell et al., 2002; Ko and Kim, 2013). The GMFM88 item scores will be summed to calculate raw and percent scores for each of the five dimensions and a total GMFM88 score. Participants will be designated as responders if they demonstrate at least 5-point increase in GMFM88 score from baseline, as assessed at the end of the 8-weeks (visit 17). Participants will be designated as non-responders if this criterion is not met. The criteria for success are defined as at least 50% of the children in the therapeutic group being classified as a responder.

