### Statistical analysis

Randomization will be stratified by age and GMFCS level. Demographics and baseline characteristics will be summarized for all patients using summary statistics for continuous variables (number of patients, mean, standard deviation, median, minimum and maximum) and using group frequencies or percentages for discrete variables. Study arms will be compared with respect to these characteristics using two-sample t-tests, binomial-based tests, chi-squared tests, or nonparametric alternatives. The primary endpoint, the GMFM88 score responder rate (i.e., >5-point increase from baseline), will be estimated and compared between groups using a two-sided chi-squared test at the 0.05 significance level. In the event of small expected cell sizes (e.g., <5), an exact test will be used. If baseline characteristics differ between study arms, logistic regression will be employed, with those characteristics, as well as stratification factors, as covariates. The secondary endpoint, the Modified Ashworth Scale (MAS) responder rate (i.e., > 0.45 change from baseline), will also be estimated and compared between treatment arms using a two-sided chi-squared test. Change-from-baseline to Phase I evaluation in MAS, GMFM88 Dimension A, B, C, D, and E, PEDI-CAT, and 10MWT (GMFCS levels I, II, and III only) will be computed for each participant as the difference between the two measurements; these will be compared between treatment groups using two-sided, two-sample *t*-tests at the 0.05 significance level. Data transformations or nonparametric methods will be substituted if the data are not found to be normally distributed. As an additional ancillary analysis, the Phase I primary, secondary, and ancillary efficacy endpoints will be compared between study arms using logistic regression, analysis of variance, or other statistical modeling appropriate to the endpoint, with stratification factors and other baseline and demographic factors as covariates. Interaction testing and subgroup analyses will be employed to investigate consistency or heterogeneity of treatment effect across subgroups based upon age, gender, race, ethnicity, clinical site, underlying condition, and/or other baseline and demographic factors. The ancillary endpoints will also be estimated in the treatment group as change from baseline to the final evaluation visit (post 8-or 16-week, visit 34), and in the control group as change from the Phase I post 8-week evaluation to the final evaluation visit (post 8 or 16-week, visit 34), with 95% confidence intervals (CI). Similar methods will be employed to characterize change from baseline (as well as change from final evaluation visit) through the follow-up phase (week 24). Safety analyses will establish frequencies of adverse events, in total and by type, along with 90% CIs. Analyses will be conducted under intent-to-treat principles. The extent of missing data will be evaluated and addressed using multiple imputation (subject to evidence supporting an assumption of Missing at Random) together with sensitivity analyses.

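### Total GMFM88 is compared between arms only as a 5-point responder rate; no mean difference is specified, and the other continuous outcomes get unadjusted t-tests first

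*Protocol article*

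**What the plan says.** Trial objectives states the hypothesis on the score itself: children given SCiP with activity-based therapy "will demonstrate a statistically greater improvement in voluntary sensorimotor function as assessed by GMFM88 scores, compared to subjects undergoing sham modality". Under Primary outcomes, item scores are "summed to calculate raw and percent scores for each of the five dimensions and a total GMFM88 score".

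In Statistical analysis the whole-scale score is then reduced to a dichotomy: "The primary endpoint, the GMFM88 score responder rate (i.e., >5-point increase from baseline), will be estimated and compared between groups using a two-sided chi-squared test". The changes compared on their continuous scale are "Change-from-baseline to Phase I evaluation in MAS, GMFM88 Dimension A, B, C, D, and E, PEDI-CAT, and 10MWT" (10MWT in GMFCS levels I to III only), and "these will be compared between treatment groups using two-sided, two-sample *t*-tests at the 0.05 significance level". The fallback is: "Data transformations or nonparametric methods will be substituted if the data are not found to be normally distributed".

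Two adjusted analyses follow in the same section. Logistic regression is used for the responder endpoint if the arms differ at baseline. An additional ancillary analysis of the primary, secondary and ancillary Phase I endpoints uses logistic regression, analysis of variance or other suitable modelling, with the stratification factors and other baseline and demographic factors as covariates.

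**The concern.** The list of continuous comparisons has all five components of the GMFM88 but not their total, and the total is the scale of the hypothesis. The pilot result that motivates the trial is also a mean GMFM88 gain, 13.3 points (Proposed solution). As written, the trial could report how many more children crossed 5 points but would have no planned estimate, with interval, of how many points were gained over sham.

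The ancillary models do not fill this gap, because the primary endpoint they cover is defined as the responder rate.

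The cut itself is worded in two ways: "Participants will be designated as responders if they demonstrate at least 5-point increase in GMFM88 score from baseline" under Primary outcomes, but more than 5 points under Statistical analysis. A child gaining exactly 5 points changes category between the two. That needs reconciling in its own right; a continuous comparison does not depend on it.

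For the outcomes that are compared as continuous changes, the first-line test uses neither the baseline value nor the age and GMFCS strata used in the randomisation. Chance baseline imbalance then stays in the estimate, and some precision is given up.

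**Working it through.** **Inputs from the article.** Sham responder rate 0.22, treatment rate 0.68, 60 participants 1:1 (30 per arm), two-sided 0.05, 10% attrition (Sample size and power). Success is defined as at least 50% responders in the therapeutic group (Primary outcomes). No SD for the change in total GMFM88 and no baseline-to-follow-up correlation is given.

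**Step 1: the article's own power figure.** Power is the sum of the binomial probabilities of all pairs of responder counts for which the test gives p ≤ 0.05.

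- 30 per arm: Pearson chi-squared 96.4%, Fisher exact 93.7%.
- 27 per arm (30 × 0.9): chi-squared 93.7%, Fisher exact 89.5%.

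The stated 80% is not reproduced, but it errs on the safe side, and the rates are worded as bounds. The responder comparison is well powered on the planned rates.

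**Step 2: responder rate against mean change.** Assume that change is normal with the same SD in both arms. The rates then imply a standardised difference d = z(p₁) − z(p₀). For 0.50 versus 0.22, d = 0 − (−0.772) = 0.772. The t-test has noncentrality d√(n/2) = 0.772 × √15 = 2.99 on 58 degrees of freedom, which gives 84% power.

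| True rates (treatment vs sham), 30 per arm | d | Chi-squared on responders | t-test on total change |
|---|---|---|---|
| 0.68 vs 0.22 (planned) | 1.24 | 96% | 99.7% |
| 0.55 vs 0.22 | 0.90 | 76% | 93% |
| 0.50 vs 0.22 | 0.77 | 62% | 84% |
| 0.68 vs 0.40 | 0.72 | 60% | 78% |

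The third row pairs the article's own success threshold of 50% with its planned sham rate. All rows below the first depart from the planning assumptions.

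**Step 3: ANCOVA against the change score.** Let σ² be the common variance at baseline and Visit 17, and ρ their correlation. Per child, the change score has variance 2σ²(1 − ρ) and the baseline-adjusted outcome has σ²(1 − ρ²). The ratio is (1 − ρ²) / [2(1 − ρ)] = (1 + ρ)/2.

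- ρ = 0.5: 0.75, a 25% reduction.
- ρ = 0.7: 0.85, a 15% reduction.
- ρ = 0.9: 0.95, a 5% reduction.

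The ratio never exceeds 1. Any gain from the strata comes on top.

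**The case against.** The strongest reply is that the article already provides most of what is asked.

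- Change is compared in all five dimensions. GMFM66, a whole-scale score from 66 of the 88 items, is an ancillary outcome and so falls under the adjusted models. On the raw scale the difference in the total is the sum of the five dimension differences. This stands against any claim that gross motor function has no continuous result. It does not supply the total: GMFM66 is a different score, and the interval for the sum cannot be had from five separate intervals.
- Strata-adjusted modelling is planned. This stands too. A reader might infer from the t-tests that baseline and strata are ignored altogether; the ancillary analysis rules that out. What remains is that it is ancillary, its model is open, and the outcome's own baseline is not named.
- The list may simply be condensed: GMFM66 and the Pediatric Balance Scale are missing from it as well, and a fuller plan may name the total. That is possible. But the article does set out a list and a first-line method, and the point is about those.
- A 5-point cut tied to the cited minimal important difference is a fair way to make the hypothesis operational, and the article reports FDA alignment on primary and secondary outcomes. Agreed; nothing here calls for changing them.
- A supportive analysis does not raise the power of the primary test or give a confirmatory claim after a failed primary. Correct. Its use is in estimation and interpretation.
- ρ may be high over 8 weeks in children spanning GMFCS I to V, which would make the ANCOVA gain small. That is plausible, and the range above includes it.

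**Conclusion.** The point holds in a limited form. No between-arm mean difference in total GMFM88 with a confidence interval is specified, although the hypothesis is written on that scale and the total is derived. The listed continuous outcomes are tested first by unadjusted change-score t-tests, with adjustment left to a loosely specified ancillary analysis.

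A reader might go further and infer that the dichotomy leaves the trial underpowered. The article does not support that: at 0.68 versus 0.22 the chi-squared test has about 96% power at 30 per arm and about 94% at 27. The advantage of the continuous comparison matters only if the true effect is smaller than planned (for example 84% against 62% at 0.50 versus 0.22). It also rests on normal change with equal SD, which the article neither states nor contradicts and which is open to doubt for a bounded scale across GMFCS I to V.

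The precision gain from baseline adjustment is 5% of variance at ρ = 0.9 and 25% at ρ = 0.5, with ρ assumed. This is an improvement at almost no cost, not an error that undermines the primary analysis.

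**What to change.** 1. Keep the responder rate as the primary endpoint and the MAS responder rate as the secondary endpoint.
2. Add a named supportive analysis: the between-arm difference in total GMFM88 at Visit 17 by ANCOVA, with baseline GMFM88, age stratum (2–7, 8–13) and GMFCS stratum (I–III, IV–V) as covariates, reported with a 95% CI. State whether the raw or the percent total is used.
3. Make the same ANCOVA form the first-line analysis for GMFM88 Dimensions A to E, MAS change, PEDI-CAT and 10MWT, each with its own baseline value, in place of the unadjusted t-tests. For 10MWT the GMFCS stratum drops out, since only levels I to III are tested.

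The fallback for non-normal data can stay, and the new analysis need not be placed ahead of MAS.

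The cost is a few lines of plan text and a little programming. Table 1 already has GMFM88, MAS, PEDI-CAT and 10MWT at baseline and Visit 17, so no visit, assessment or participant is added. The wording should be fixed before unblinding, because the same analysis added later would be post hoc.

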
## Data management and safety

Parents and/or legal guardians of all eligible participants will be invited to discuss the protocol and its risks and benefits with the site Principal Investigator (PI). Parents and/or legal guardians of potential participants will be given at least 72 h and will be encouraged to read the informed consent, and discuss the study with their child, physician, family, and friends, before signing the IRB-approved informed consent. The informed consent forms will be written in a language understood by an eighth-grade student and will contain information on all outcomes as well as PI’s contact information. IRB-approved age-appropriate assent forms will be provided to minors, based on considerations such as the age, maturity, and degree of literacy. Assent from pre/non-literate children will be obtained in accordance with local IRB requirements.

The original signed informed consent (and assent, if applicable) and two copies will be kept in the PI’s office. No participant will be allowed to enroll without being examined by site PI. The participants will be monitored closely to assess for evidence of complication from experimental protocol. The data monitor, clinical research operations team and medical monitor will closely monitor the participants in regards to the procedures and will be available for consultation.

During training, every participant will be slowly acclimated to the treadmill and other devices. Vitals will be monitored (blood pressure, oxygen saturation, heart rate, pain scores) at each session. Stimulation will be stopped in case of an adverse event during and the participant will receive appropriate standard of care treatment. Before and after every session, a physical therapist will examine the participant’s skin for irritations and abrasions. If skin irritations or abrasions are caused by the recording electrodes or hand placements of trainers, electrode and hand placement will be modified. Furthermore, the therapist will monitor the participant’s skin and muscle for signs of muscle strain, joint sprain, and skin irritation (e.g., temperature and redness). The therapist will assess the appropriate lower extremity parameters and monitor manual assistance by trainers to avoid joint sprain. The physical therapist or trained staff member will stretch the muscles of the participants before and after each training session to prevent injury. PAICP will be completed at every session to monitor for pain signs.

To protect confidentiality, each participant will be assigned a coded identification number for all evaluations and analyses. Data (including video files) will be reported using an electronic data capture system (EDC). Original video files and physical materials will be secured in a locked storage area of the laboratory. Only members of the research team will have access to the data for analyses. SpineX team will meet regularly with the contract research organization.

Adverse events (AE), Adverse Device Effect (ADE) and Device Deficiency (DD) will be reported in a timely manner via electronic CRFs, and will be reported to the Institutional Review Board in accordance with local requirements. Serious Adverse Events (SAE), Series Adverse Device Effect (SADE), and Unanticipated Adverse Device Effects (UADEs) will be reported to IRBs, investigators, and the U.S. FDA in accordance with applicable regulatory requirements. All adverse events will be classified based on their severities as either mild, moderate or severe. Protocol amendments, if applicable, will be approved prior to implementation by overseeing IRBs. An immediate change of protocol will be made in the case of serious, unexpected events. If a change is required, this may be implemented to protect the welfare of the participant prior to obtaining IRB approval. However, every effort will be made to contact the IRB and request approval prior to implementation. Based on our pilot studies (Edgerton et al., 2021; Gad et al., 2021; Hastings et al., 2022), the anticipated adverse events are listed in Table 3.

**Table 3 tab3:** Summary of anticipated adverse events.

Adverse event	Likelihood
Skin breakage around the site of stimulation	Rare
Changes in blood pressure	Likely
Skin irritation, discoloration or pain around the site of stimulation	Unlikely
Skin irritation due to placement of trainers’ hand	Likely
Electric shock	Unlikely
Sore muscles	Unlikely
Burns	Unlikely
Tingling of extremities during and after the session	Likely
Increased heart rate	Likely
Light-headedness and dizziness	Rare

## Ethics and dissemination

The trial will be conducted in accordance with the Declaration of Helsinki and the International Conference on Harmonization Good Clinical Practice Guidelines, and applicable regulatory requirements (Goodyear et al., 2007). Central and site level ethical approval will be obtained via the central IRB or local IRBs prior to enrollments. The proposed trial is registered on clinicaltrials.gov (NCT05720208).

Informed consent forms will include language noting that the trial and its results will be shared on ClinicalTrials.gov. Each clinical site will be registered and will provide results to ClinicalTrials.gov in compliance with NIH Policy. The final study report will be submitted to US FDA and all data including study results will be uploaded to the ClinicalTrials.gov database. The results will also be published in relevant scientific journals.

We will undertake initiatives to reach medical professionals external to the trial and introduce them to the application of SCiP™ by virtual and in-person workshops at clinical sites or scientific conferences. Every effort will be made to facilitate implementation and replication of the trial on global scale via our well-established network of collaborations. The long-term goal of this trial is the transition of this novel treatment into clinical practice. The key steps in this process will include: (1) obtaining clinical approval from FDA for SCiP™ as a therapeutic indication to promote motor recovery in children with CP; (2) developing the clinical practice guidelines and reimbursement billing codes for this therapy; and (3) educating medical professionals as well as consumers on the delivery, benefits and any potential side effects of this novel therapy.

## Data availability statement

The original contributions presented in the study are included in the article/Supplementary material, further inquiries can be directed to the corresponding author.

